### Exclusion criteria

Patients with any of the following conditions will be excluded: 1) urinary dysfunction caused by gonorrhea or urinary tract infection; 2) oliguria and anuria caused by urinary calculi, prostate cancer, bladder tumor and acute/chronic renal failure; 3) urinary dysfunction caused by neurogenic bladder, bladder neck fibrotic and urethral stricture; 4) failure of invasive therapy for prostatic obstruction; 5) injured local organs, muscle and nerve caused by pelvic operation or trauma; 6) upper urinary obstruction and hydrocele combined with damaged renal function due to BPH diagnosed by B-ultrasound; 7) Patients unable to commit to treatment because of commuting problems to the hospital.

### Interventions

In addition to records in ancient books [19], we also choose this acupuncture point according to our published study [13,14] and a consensus with acupuncture experts in Beijing. Huatuo Brand needle (0.3*100 mm, Suzhou Medical Appliance Factory CL) and G6805-2 electric stimulator (Shanghai Huayi Medical Instrument Co.Ltd) will be used in the trial.

#### Treatment group

Needle at bilateral BL33 with a 45°angle. A feeling of soreness and distension will be felt when needling into the 3rd posterior sacral foramina (S3) and finally with radiation of sensation to the perineum. Needle 60-80 mm without lifting, thrusting or rotating. Put on the electric stimulator with a disperse-dense wave, 20Hz. The current intensity is increased to the patients' maximum tolerance and then slightly reduced to a bearable level.

#### Control group

Take the site 2 *cun *lateral BL33 as the non-point (Figure 2) for the control group. Manipulation methods and electric stimulator parameters are the same with those of the treatment group. The pilot study shows that patients in the control group have the same feeling with those of the treatment group.

**Figure 2 F2:**
[figure not shown]
**BL33 and non-point used in the trial**.

There are 16 sessions for all patients (5 sessions in the 1^st ^and 2^nd ^weeks, 3 sessions in the 3^rd ^and 4^th ^weeks) and each session last 30 minutes. Acupuncture for the two groups will be operated by the same acupuncturist with more than ten years of experience. This acupuncturist is blinded to the outcome assessment at baseline, the 6^th ^week and the 18^th ^week.

### Outcome measures

The primary outcome measure is reduction of international prostate symptom score (IPSS) at the 6th week compared with baseline. The secondary outcome measures are reduction of bladder residual urine, increase in maximum urinary flow rate at the 6th week and reduction of IPSS at the 18^th ^week.

Safety evaluation is based on adverse events which include hematoma, fainting, severe pain, and local infection. Any adverse event and the time and measures to take will be recorded in detail during treatment.

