## 2. Methods and Design

### 2.1 Design

This study is a prospective randomized controlled trial and will be completed in Acupuncture Department of Guang'anmen Hospital affiliated to China Academy of Chinese Medical Sciences from Sep. 2010 to July 2012. Randomization is performed by Drug Clinical Trial Office affiliated to Guang'anmen Hospital. Computer-made opaque sealed envelopes are numbered consecutively. All of the envelopes are preserved by an investigator (who is uninvolved in acupuncture operation and data analysis). After the baseline assessment has been carried out and the informed consent has been obtained, an envelope is opened by the investigator according to patient's sequence entering the trial and the allocated treatment regimen is offered to the clinician. Two copies of the envelopes will be kept to guard against researchers trying to change the randomization.

Participants are recruited from PBH clinic in the hospital by the use of local newspaper advertisements and posted notices at clinic site. Patients on mediciation for urinary symptoms are requested to stop medication one week before baseline assessment. Before randomization, patients will complete 1-week baseline assessment which includes IPSS, bladder residual urine and maximum urinary flow rate and they will be divided into three groups according to their IPSS score, i.e. the mild group (0-7), moderate group (8-19) and the severe group (20-35). Patients belonging to the severe group will be excluded.

Enrolled patients will be randomized into the treatment group or the control group. The diagnosis and assessment will be made by an independent urologist who is uninvolved in the treatment process. Acupuncture will be given 5 sessions/week in the first two weeks and 3 sessions/week in the third and the fourth weeks, a total of 16 sessions.

The trial protocol is in accordance with the principles of the Declaration of Helsinki and has been approved by the review board and ethics committee of the hospital. Participants will be requested to sign an informed consent before any treatment is given. All patients have right to decide whether they would sign up or not and they can withdraw from the trial at any time (Figure 1).

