**Figure 3 F3:**
[figure not shown]
**Effects of BL33 acupuncture and non-point acupuncture of this trial**.

This study will follow rigorous methodological requirements. The staffs in charge of assessment and statistician are all blinded to the patients' allocation. Acupuncture operation(performed by an experienced acupuncturist)and filling of case report (by a postgraduate) form will be done under strict supervision. Phone calls and e-mails will be used to inform the patients for follow-up assessment which will be done at their homes or in the clinic. Any medicine taken and other treatment conducted during this time will be recorded in detail.

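### Adverse event recording is stated for the treatment period (weeks 1 to 4), although patients are followed to week 18

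*Protocol article*

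**What the plan says.** The safety paragraph under Outcome measures has two sentences. The first gives the content: "Safety evaluation is based on adverse events which include hematoma, fainting, severe pain, and local infection". The second gives the scope and the period: "Any adverse event and the time and measures to take will be recorded in detail during treatment".

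The treatment period is fixed in section 2.1 as "5 sessions/week in the first two weeks and 3 sessions/week in the third and the fourth weeks, a total of 16 sessions", and the Interventions text repeats that schedule. The end of follow-up is clear from the same Interventions text: "This acupuncturist is blinded to the outcome assessment at baseline, the 6^th ^week and the 18^th ^week".

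Two other places describe records that run on after treatment. The Quality control section keeps drop-outs, withdrawals with their reasons, and compliance across both treatment and follow-up. The Discussion, directly after explaining how patients will be contacted for follow-up assessment, adds: "Any medicine taken and other treatment conducted during this time will be recorded in detail".

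**The concern.** The article gives a collection period for adverse events, and that period ends before the primary endpoint is measured. This is a stated rule rather than a detail left out of a condensed article, so it can be judged as written. Where the authors intend a record to cover the whole study, they say so. For adverse events they use the narrower period.

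Two of the four named events, local infection and hematoma, can become apparent some time after a session. After the last session there is no further treatment visit at which to note them. Staff following the article would record a medicine taken in follow-up but would have no instruction to record the event that led to it. Both arms receive deep needling (60-80 mm) with electrical stimulation, at different sites, so a comparison of harms by arm is a reasonable thing to want from the trial. Under the present wording it would describe weeks 1 to 4.

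**Working it through.** **Inputs**
- Sessions: 5 per week for 2 weeks, then 3 per week for 2 weeks (section 2.1; Interventions).
- Assessments: baseline, week 6 and week 18 (Interventions; Outcome measures).
- Stated adverse event window: the treatment period (Outcome measures).
- Assumption: weeks 6 and 18 are counted from the start of treatment. The article does not state the origin.

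**Reproducing the plan's own figure**
- Sessions = 5 × 2 + 3 × 2 = 16, as stated, in 2 + 2 = 4 weeks.

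**Length of the gap**
- From the end of treatment to the primary assessment: 6 − 4 = 2 weeks.
- From the end of treatment to the last assessment: 18 − 4 = 14 weeks.

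A different origin for the week count would move these gaps slightly. Both outcome assessments would still come after treatment.

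**What is recorded, and when**
- Adverse events: stated for treatment; nothing stated for weeks 5 to 18 (Outcome measures).
- Drop-outs, withdrawals with reasons, compliance: treatment and follow-up (Quality control).
- Medicines and other treatment: follow-up, on the natural reading of the time reference (Discussion).
- IPSS: weeks 6 and 18. Residual urine and maximum flow rate: week 6 (Outcome measures).

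**Applying the rules to an event after session 16**
1. An infection treated with a medicine: the medicine is recorded; the event has no stated entry.
2. A hematoma that leads to withdrawal: the reason is recorded; the event has no stated entry.
3. A hematoma or infection that is untreated in a man who stays in the study: none of the stated records is bound to capture it.

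In cases 1 and 2 something can be reconstructed, though not reliably the nature and timing of the event. Case 3 is the actual gap.

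**The case against.** The strongest reply is that the sentence does not say adverse events are recorded *only* in treatment, that other follow-up records exist, and that the unseen full protocol may set a longer window. The named events are mostly acute consequences of needling, expected at or soon after a session and so mostly inside the window. The trial's aim is point specificity, and its primary and secondary outcomes are all efficacy measures.

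Much of this stands, and it limits the point. Several stronger readings are tempting, and the article does not support them:

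- *That follow-up has no safety recording.* Withdrawal reasons, medicines and other treatment are recorded, and urinary worsening would show in part through IPSS and, at week 6, residual urine and flow rate.
- *That late events will be missed.* The article gives no late-event rate. They may be missed.
- *That 14/18 = 78% measures the loss.* It is a share of calendar time. The risk of needling events is concentrated around the sessions, so the share of events outside the window could be far smaller.
- *That only the four named events count.* The list is introduced as non-exhaustive, and the next sentence covers any adverse event. The scope is adequate; the period is the problem.
- *That the medication-free run-in is part of the gap.* Patients on urinary medication are "requested to stop medication one week before baseline assessment", and "Before randomization, patients will complete 1-week baseline assessment". All of this precedes needling and allocation, so events there belong to neither arm and cannot distort the comparison. A condensed article may leave their handling to the full protocol.

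The reply does not remove the contrast between the stated periods: adverse events are tied to treatment, while other records run into follow-up. If the full protocol has a longer window, the article's sentence should be brought into line with it.

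**Conclusion.** The point holds as a modest one. The stated adverse event window is the 4-week treatment period, patients are followed to week 18, and nothing in the article carries adverse event recording to the week-6 or week-18 contacts. An event that appears after the last session may have no adverse event entry, and a comparison of harms by arm would cover the treatment period only.

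In calendar terms the gap is 2 weeks to the primary assessment and 14 weeks to the last, assuming weeks are counted from the start of treatment. The number of events at stake cannot be estimated from the article. The main exposure is probably a short tail after session 16, on the assumption that needling events arise at or soon after a session. The primary analysis, the sample size, the power and the significance level are unaffected.

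**What to change.** Replace the recording sentence under Outcome measures with one to this effect: *any adverse event, with its timing and the measures taken, will be recorded from the first session to the week-18 assessment; patients will be asked at each session and at the week-6 and week-18 contacts; events will be reported by arm, separately for the treatment and follow-up periods.*

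This brings adverse events into line with the follow-up records described under Quality control and in the Discussion. It uses contacts that already exist, and the split by period keeps the on-treatment comparison visible. The cost is one sentence, one question and a form page at each of two contacts, and a few more events to report. No extra visits or patients are needed.

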### Statistical analysis

The statistical analysis will be performed by a statistician blinded to allocation in Clinical Evaluation Center of China Academy of Chinese Medical Sciences. Statistical analyses will be performed using the SPSS statistical package program (ver.16.0) and the level of significance will be established at α < 0.05. The data analysis of baseline characteristics is based on the intention-to-treat (ITT) population (data of all participants who are randomized will be analyzed). The data analysis of the primary and secondary outcomes is mainly based on the ITT population. In addition, the data analysis of the primary outcome is also based on per-protocol (PP) population as a supportive analysis.

For primary and secondary outcome measures, analysis of covariance will be used to investigate whether BL33 acupuncture is more effective than non-acupoint acupuncture.

### Quality control

Before the trial, all staff involved will be trained in patients selection and exclusion, filling up of the case report and acupuncture method. During the trial, supervisors will check on case reports, and acupuncture operation twice a month. Drop-outs, withdrawals (and the reasons), the compliance of all patients will be recorded in detail throughout the treatment and follow-up period.

## Discussion

The point specificity has been a controversial research topic for a long time [20] and it has become a point of contention since the publication of those trials [5-8] in Germany as previously mentioned. But from the viewpoint of Nanna Goldman [9], anti-nociceptive effect of acupuncture is a general reaction to the mechanical stimulation leading to the belief that pain syndrome should not be used in point specificity study at the present time.

The reasons we choose BPH for point specificity include: 1) studies show that acupoints have specific effect in regulating function of zang-fu organs [10-12] and BPH is appropriate for this kind of study; 2) our previous study shows that electroacupuncture has effect in improving the symptoms of BPH and the effect is better than that of non-acupoint acupuncture; 3) a single point acupuncture is most suited for point specificity study.

In this trial, points used here are on the back area where patients unable to see and patients of the two groups have the same feeling because the manipulation methods are all the same. So patients are blinded as to which treatment they will receive. As the manipulation methods of the two groups are the same, the different effects between the two groups will be completely produced by point location, which will give a good explanation of point specificity. And also the placebo effect could be excluded and the specific effect of electroacupuncture at BL33 could be investigated. As electroacupuncture is also used in the control group with the same parameter and same insertion depth, part of treatment effect could be achieved. So part of specific effect of the treatment group will be excluded inevitably (Figure 3).

**Figure 3 F3:**
[figure not shown]
**Effects of BL33 acupuncture and non-point acupuncture of this trial**.

This study will follow rigorous methodological requirements. The staffs in charge of assessment and statistician are all blinded to the patients' allocation. Acupuncture operation(performed by an experienced acupuncturist)and filling of case report (by a postgraduate) form will be done under strict supervision. Phone calls and e-mails will be used to inform the patients for follow-up assessment which will be done at their homes or in the clinic. Any medicine taken and other treatment conducted during this time will be recorded in detail.

## Conclusion

The aim of this study is to investigate whether BL33 acupuncture is more effective than non-acupoint acupuncture, i.e. point specificity of BL33 for BPH.
